#### Qualitative Analysis

Focus groups consisting of both cohorts will be conducted. For referred participants, the association between their perceived risk of LC based on both their genetic perceptions of risk and their actual clinical risk of LC and undertaking preventative behaviors and screening will be explored.

First, focus groups consisting of both cohorts will be audiovisually recorded and transcribed in verbatims. Responses will be labeled with descriptive codes by 2 independent analysts using NVivo (Lumivero). Interrater agreement and κ coefficients will be calculated to assess intercoder reliability and consensus reached through comparison and discussion within the panel group. The second stage will involve constant comparison, where codes and their content are compared across interviews to discern common and divergent themes. In the final stage, the data will be organized by searching for patterns, variations, and relationships between themes to characterize the entire dataset.

### Sample Size

Preliminary data from the provincial LC screening program indicate that 40% of patients either referred to the program by their primary care physician or via self-referral meet the eligibility criteria for LC screening. The McGill University Health Centre receives approximately 800 new patients with LC annually, and the provincial LC screening program receives around 100 referrals each month. With a sample size of 194 referred participants, we will be able to detect a 20% difference in the rates of referral, with a power of 80% and an α value of .05.

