**Secondary outcomes**			
	Proportion of participants eligible for the Quebec provincial LC screening program	Questionnaire: cohort 2 PLCOm2012 model	
	Proportion of participants eligible for screening who complete LDCT^b^ screening within 18 months from referral	Provincial health data	
	Proportion of participants who demonstrate interest in undergoing genetic testing to inform their LC risk	Questionnaire: cohort 2	
	Proportion of individuals who demonstrate interest in a smoking cessation program among referred participants who are current smokers	Questionnaire: cohort 2	
	Barriers and facilitators in the uptake of LC screening and preventative strategies, based on perceived LC risk	Focus groups: cohort 1 and cohort 2	
	Number of visitors on the study’s website for referred participants	Google analytics data	

^a^LC: lung cancer.

^b^LDCT: low-dose chest tomography.

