### Statistical Analysis

#### Quantitative Analysis

Participants with LC who refer at least one peer for participation will be compared to those who did not refer a peer for participation. To identify the predictive factors of referral, multivariable logistic regression will be used, adjusting for age, sex, educational attainment, health literacy, PAM score, and phase of LC trajectory. The dependent variable in the logistic regression will be referral by patients with LC. Using logistic regression, we will also examine if increased patient with LC activation is associated with increased odds of referral. Chi-square tests and 2-tailed *t* tests will be used for comparisons of categorical and continuous variables.

Referred participants who are eligible for LC screening will be considered as cases. A control group will be selected from patients who were either self-referred or referred by their primary care physician to the Quebec LC screening program and matched by age (1:1). To determine if participants in cohort 2 have a higher risk of LC than the controls, the mean PLCOm2012 scores will be compared using 2-tailed *t* tests in our cohort and in the Quebec LC screening program. The predictive factors of being eligible for LC screening and whether being referred by survivors of LC is associated with increased odds of being eligible will be examined using multivariable logistic regression. We will account for clustering among individuals referred by the same family member using a random effect model.

Spearman coefficients will be calculated to assess the correlations between the actual risk and the perceived risk of LC. Kruskal-Wallis tests will be used to compare actual and perceived risks of LC with different levels of anxiety. Odds ratios and their 95% CIs will be reported. All statistical analyses will be conducted using R (version 4.2.0; R Foundation for Statistical Computing).

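### The power statement mislabels its unit and its endpoint: 194 is reproduced as a two-group total for the proportion eligible, not as the number of referred participants for a referral rate

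*Protocol article*

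**What the plan says.** The Sample Size section gives one reference rate: "40% of patients either referred to the program by their primary care physician or via self-referral meet the eligibility criteria for LC screening". It then states: "With a sample size of 194 referred participants, we will be able to detect a 20% difference in the rates of referral". The power attached to this claim is 80%, at an α of .05. The section does not say whether the 20% is absolute or relative, whether the test is two-sided, or how many controls there are.

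Three other places bear on how this is read:

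- Data Collection, Cohort 2, uses referred participants as the name for cohort 2, the people referred by patients with lung cancer.
- Quantitative Analysis adds a separate comparator: "A control group will be selected from patients who were either self-referred or referred by their primary care physician to the Quebec LC screening program", matched 1:1 on age. The cases are the referred participants who are eligible for screening. The same paragraph plans a logistic regression of eligibility on survivor referral, with a random effect for contacts of the same referrer.
- Table 1 lists as a secondary outcome: "Proportion of participants eligible for the Quebec provincial LC screening program". The primary outcomes are the number referred per survivor and the mean lung cancer risk of those referred.

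Results reports that enrollment ran from June 2023 to January 2024, with 25 survivors and 84 referred contacts.

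**The concern.** A power statement has to tie a number of people to a named group and a named endpoint. Here neither tie matches the inputs.

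**Unit.** The article's usage puts all 194 in cohort 2. The inputs yield 194 only as the sum of two equal groups.

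**Endpoint.** The 40% is an eligibility proportion, while the difference is said to be in referral rates. The article gives no reference rate of referral. None is available from the controls, who all reached the program by self-referral or through a physician. The wording also invites confusion with a different analysis in Quantitative Analysis, where referral by the patient with lung cancer is the dependent variable in cohort 1.

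Results are still to be published. A reader who takes the section at face value will think a referral rate was powered, and will judge the 84 contacts against a cohort 2 target of 194.

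**Working it through.** **Inputs.** From Sample Size: p1 = 0.40, difference 0.20, power 0.80, α = 0.05. From Quantitative Analysis: 1:1. Assumed: two-sided, difference in percentage points (p2 = 0.60), independent observations, age matching ignored.

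**1. Reproduce 194.** Pooled-variance formula for two proportions:

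n per group = [z(0.975)·√(2·p̄·(1−p̄)) + z(0.80)·√(p1(1−p1) + p2(1−p2))]² / (p2−p1)²

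With p̄ = 0.50:

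- 1.960 × √0.50 = 1.386
- 0.842 × √0.48 = 0.583
- (1.386 + 0.583)² / 0.04 = 96.9, so **97 per group and 194 in total**

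The arcsine formula also gives 97 per group.

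**2. Try other readings.**

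| Reading | Per group | Total |
|---|---|---|
| 40% vs 60%, unpooled variance | 95 | 190 |
| 40% vs 60%, continuity-corrected | 107 | 214 |
| 40% vs 60%, one-sided | 77 | 154 |
| 40% vs 20% | 82 | 164 |
| 40% vs 48% (20% relative) | 604 | 1208 |
| One sample, 40% vs 60% | – | 48 |
| One sample, 40% vs 50% | – | 191 |

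No 1:1 reading with a 20-point difference puts 194 in the referred group alone. Three referred per control (195 and 65) comes close but contradicts the 1:1 ratio. The one-sample 191 is near 194 but rests on a 10-point difference.

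**3. Take the sentence literally.** Power = Φ[(0.20·√n − 1.386) / 0.693].

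- n = 97: (1.970 − 1.386) / 0.693 = 0.84, power 80.0%
- n = 194: (2.786 − 1.386) / 0.693 = 2.02, power 97.8%

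With 194 per group, 80% power is already reached at a difference of about 14 points.

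**4. Identify the endpoint.** The 40% has program referrals as its denominator and meeting the eligibility criteria as its numerator. The matching quantity in cohort 2 is the proportion eligible, the first secondary outcome in Table 1.

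**5. Check the comparator.** If the cases are only the eligible referred participants, 100% of them are eligible by construction. That set cannot supply the 60% in a comparison of proportions eligible. The comparison needs all survivor-referred participants against program referrals before selection on eligibility, which is the population the 40% describes.

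**6. Allow for clustering.** Mean contacts per survivor = 84 / 25 = 3.36. Design effect = 1 + (3.36 − 1) × ICC, before any allowance for unequal cluster sizes. The article gives no ICC, so these values are assumptions:

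| Assumed ICC | Design effect | Referred participants matching 97 independent ones |
|---|---|---|
| 0.1 | 1.236 | 120 |
| 0.2 | 1.472 | 143 |
| 0.4 | 1.944 | 189 |

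**7. Relate to enrollment.** 84 / 194 = 43% and 84 / 97 = 87%. With 84 per group, power for 40% versus 60% is Φ[(1.833 − 1.386) / 0.693] = Φ(0.645), about 74%, before clustering.

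**The case against.** The article does not show how 194 was derived, so 97 + 97 is an inference. The program's own patients are also called referred in the Sample Size section, so the 194 could loosely cover both groups. That looser reading runs against the article's use of the term for cohort 2, and it still makes 194 the two-group total, so the sentence needs rewording either way. What stands is that the original calculation should be checked before the text is changed.

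A reader might infer that the referred-cohort target is twice what the study needs. The documents do not support this. It would hold only if contacts of the same survivor were independent, and Quantitative Analysis plans for them not to be. Under the assumed ICCs of 0.1 to 0.4, the equivalent of 97 independent participants is 120 to 189, the upper end close to 194.

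A reader might also fault the article for giving no precision figures for the two primary outcomes. They are descriptive outcomes in what the Discussion calls a pilot study, and a condensed article may leave such figures to the full protocol.

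Finally, recruitment is over, no planned analysis method depends on the sentence, and 84 falls short on either reading. That limits the harm but does not make the statement correct.

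**Conclusion.** The section is wrong as written on two labels, while its arithmetic is sound. The 194 is exactly the total for two groups of 97 comparing 40% with 60% eligible, at two-sided 5% and 80% power. It is not the size of cohort 2 under those inputs; with 194 in each group, power would be 97.8%. The powered quantity is the secondary eligibility outcome, not a rate of referral.

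This rests on a two-sided test, an absolute 20-point difference, 1:1 groups and independent observations. The first two are not stated but are what reproduces 194. The 1:1 ratio comes from matching described for eligible cases, so the comparator for the proportion eligible remains for the authors to state. Clustering by survivor makes real power lower than the independent-observation figures, by an amount the article does not allow one to fix.

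**What to change.** After checking the original calculation, restate the Sample Size section along these lines:

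> A total of 194 people (97 referred by survivors and 97 provincial-program referrals not selected on eligibility) gives 80% power at a two-sided 5% level to detect 60% versus 40% meeting the screening eligibility criteria, a difference of 20 percentage points, assuming independent observations. This concerns the secondary outcome of eligibility.

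Then:

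- reconcile this comparator with Quantitative Analysis, where 1:1 age matching is tied to cases who are already eligible;
- say that power falls once contacts of the same survivor are correlated, and show the range above with its ICCs labeled as assumptions;
- disclose that the correction was made after enrollment closed at 84 referred contacts, with about 74% power at 84 per group before clustering. The restatement moves apparent attainment from 43% to 87%, so it should not be made silently.

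The cost is a look at the original calculation and a few sentences. Settling the comparator may take more than wording if data on program referrals not selected on eligibility have not been arranged. The program's intake of around 100 referrals a month suggests that numbers are not the obstacle.

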### Ethical Considerations

This study has been approved by the McGill University Health Centre’s Research Ethics Board (MP-37-2023-9041). All participants will provide their informed consent before participation and will be informed that they can withdraw from this study at any time. Informed consent is obtained in either the English or French language through (1) internet-based web forms, (2) phone calls with trained research staff, or (3) completing consent forms in person when approached in one of this study’s clinics. To ensure participants fully understand this study’s goals when they enroll, three simple comprehension questions are asked being: (1) if this study involves medications (false), (2) if participants will be asked to complete questionnaires (true), and (3) whether they will be asked to refer family and friends (true). If participants have any questions or concerns regarding this study, they can contact our research team via telephone or email at any time (contact information is available on this study’s website, pamphlets, and posters).

The REDCap platform used to collect data conforms to the General Data Protection Regulation and Canadian privacy legal and security standards. Access to the REDCap platform is secured with private log-ins and 2-factor authentication. The REDCap database is securely hosted on the Research Institute of the McGill University Health Centre server. No information will be released to unauthorized third parties without prior written approval of the participant except as necessary for monitoring by public health authorities or our institutional research board. Participants will not receive compensation for their enrollment in this study. Those participating in focus groups will be reimbursed on an hourly basis by the Research Institute of the McGill University Health Centre.

## Results

Enrollment in the cohorts was conducted from June 2023 to January 2024, with participants being followed up through July 2025. Overall, we have enrolled 25 survivors of LC who have referred 84 of their close contacts to this study. The results of this study are expected to be reported at the end of 2025 through publications in peer-reviewed journals and presentations at relevant national and international conferences.

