**Results:**

Overall, 25 survivors of LC and 84 close contacts were enrolled from June 2023 to January 2024, with followed up through July 2025. The results are expected by the end of 2025.

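### The 80% power claim is left standing although enrolment closed at 84 contacts against the 97 per group it needs, and the calculation makes no allowance for clustering by survivor

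*Protocol article*

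**What the plan says.** The Sample Size section of the protocol article starts from a usual-care rate: "40% of patients either referred to the program by their primary care physician or via self-referral meet the eligibility criteria for LC screening". Its power statement sets alpha at 0.05 and power at 80%, and names the target effect: "we will be able to detect a 20% difference in the rates of referral". The number it attaches to this is 194, described as people who were referred. It gives no intracluster correlation, design effect or other inflation.

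The Quantitative Analysis section plans for correlated observations: "We will account for clustering among individuals referred by the same family member using a random effect model". It also specifies an age-matched control group from the provincial program at 1:1, with the eligible referred participants as cases.

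The Results section gives an enrolment period of June 2023 to January 2024, in the past tense, and reports: "Overall, we have enrolled 25 survivors of LC who have referred 84 of their close contacts to this study". The Abstract agrees: "25 survivors of LC and 84 close contacts were enrolled from June 2023 to January 2024". Neither these sections nor the Limitations section revisits the sample size or the power.

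**The concern.** The article carries a forward-looking power claim and, a few sections later, a closed enrolment that cannot support it. There are two separate gaps. Fewer people were enrolled in the referred group than the calculation requires. The calculation also treats referred people as independent, while the analysis plan accepts that those referred by one survivor are not. Each lowers power below the stated 80%.

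At stake is how the between-group comparison of screening eligibility will be read. If the 80% figure remains the only power statement, a non-significant result could be taken as coming from an adequately powered comparison.

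**Working it through.** **Inputs from the article.** Control proportion 40%; difference 20%, read as percentage points (40% vs 60%); power 80%; alpha 0.05; 25 survivors and 84 contacts. The power statement does not give sidedness; two-sided reproduces the figure and matches the 2-tailed *t* tests planned elsewhere.

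**Inputs assumed here.** ICC 0.1 to 0.3; CV of cluster size 0 or 0.8; 84 controls (1:1). The article gives no value for the first two, and its 1:1 rule is stated for eligible cases.

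**1. Reproduce 194.** For two proportions with pooled variance under the null and no continuity correction:

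n per group = [1.96 × √(2 × 0.5 × 0.5) + 0.8416 × √(0.4 × 0.6 + 0.6 × 0.4)]² / 0.20² = 96.9, rounded up to 97.

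2 × 97 = 194. The stated number is therefore the two-group total for independent observations. Taken literally, 194 referred plus 194 controls would give about 98% power, not 80%. Other readings do not give 194: one-sided 154, continuity-corrected 214, 40% vs 20% 164, and a 20% relative increase (40% vs 48%) 1208.

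**2. Shortfall.** Referred participants needed: 97. Enrolled: 84. Difference: 13; 84/97 = 87%.

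**3. Power at 84 vs 84, independent.**
- SE under the null = √(0.25 × 2/84) = 0.0772
- SE under the alternative = √(0.24 × 2/84) = 0.0756
- z = (0.20 − 1.96 × 0.0772)/0.0756 = 0.645, so power = 74.1%

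**4. Clustering, referred group only** (controls are not clustered by survivor). Mean cluster size = 84/25 = 3.36. Design effect = 1 + [(1 + CV²) × 3.36 − 1] × ICC. Effective referred n = 84 / design effect, compared with 84 controls. The last column is the difference detectable at 80% power from a 40% control rate.

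| ICC (assumed) | CV (assumed) | Design effect | Effective n | Power | Detectable difference |
|---|---|---|---|---|---|
| 0 | – | 1.00 | 84.0 | 74.1% | 21.5 points |
| 0.1 | 0 | 1.24 | 68.0 | 69.2% | 22.7 |
| 0.2 | 0 | 1.47 | 57.1 | 64.8% | 23.8 |
| 0.3 | 0 | 1.71 | 49.2 | 60.9% | 24.9 |
| 0.1 | 0.8 | 1.45 | 57.9 | 65.2% | 23.7 |
| 0.2 | 0.8 | 1.90 | 44.2 | 57.9% | 25.7 |
| 0.3 | 0.8 | 2.35 | 35.7 | 52.0% | 27.6 |

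**5. The clustering gap without under-enrolment.** At the planned 97 vs 97 with equal clusters, ICC 0.1 to 0.3 gives 75.5% to 67.2%. Reaching 97 would not by itself have delivered 80%.

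**6. Dependence on 84 controls.** With 84 independent referred participants, 115 controls restore 80%. With equal clusters, about 167 are needed at ICC 0.1, 296 at 0.2 and 1235 at 0.3. At ICC 0.3 and CV 0.8, 800 controls give only about 66%.

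**The case against.** The Sample Size section is the prospective rationale, and the Results section reports the achieved numbers openly. The Discussion calls the study a pilot of acceptability and feasibility. Eligibility is a secondary outcome; the calculation does not address either primary outcome. The analysis already includes a random effect and odds ratios with 95% CIs, so clustering is missing from the sample size only. The independent-case loss is modest: 80% to 74%, or 20 to 21.5 detectable points. The number of controls is not firmly fixed at 84, and the provincial program receives about 100 referrals a month.

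Much of this stands, and it limits the size of the point. It does not remove it. The article makes a formal power claim for a between-group comparison and never says that the numbers behind it were not reached. A pilot label does not make an unattained figure correct. A random effect in the model gives an appropriately wider interval but does not restore the power. Extra controls help at low ICC but not at the pessimistic end of the range.

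Three stronger readings are tempting and are not supported:
- **That only 43% of the target was enrolled (84/194).** This sets one group against a two-group total. The like-for-like figure is 87%.
- **That the design delivers 52-74% power as a matter of fact.** Only the 74% follows from the article's figures, given 1:1 controls. The 52% needs both an ICC of 0.3 and a CV of 0.8, and neither is in the article.
- **That power is 38-52% because only the 34-50 eligible people count as cases.** Eligibility cannot be compared at 60% vs 40% among people who are all eligible. For that group the article plans a comparison of mean PLCOm2012 scores and gives no standard deviation from which to compute power.

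**Conclusion.** The point holds. The 80% claim rests on 97 referred participants and 97 controls, all independent. The study closed at 84 referred participants in 25 clusters, and the claim was not revised. The figure of 194 is also mislabelled as referred participants.

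Two parts need no assumed ICC: the 13-person shortfall, and power of about 74% with 84 controls, which takes the 20% as an absolute difference above 40%. That clustering lowers power further follows from the plan's own expectation of correlated contacts, but by how much is assumption-dependent: about 69-61% with equal clusters at ICC 0.1 to 0.3, and about 65-52% if cluster sizes also vary with CV 0.8. The detectable difference at 80% power is about 21.5 points if independent, 23-25 points with equal clusters, and up to about 27.6 points at the most pessimistic combination.

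A reader might infer that the authors would present a null result as evidence of no difference. The article does not say so. The risk is that nothing in it guards against that reading.

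**What to change.** In the Sample Size section, keep the target as the planned figure and correct its label to 194 in total, 97 per group, for independent observations.

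Add the achieved design, for example: enrolment closed with 84 referred participants in 25 clusters; with 84 controls this gives about 74% power for 60% vs 40% before clustering, about 69-61% at an assumed ICC of 0.1 to 0.3 with equal clusters, and about 65-52% if cluster sizes vary with an assumed CV of 0.8. Once the data are in, replace the assumed CV with the observed spread of referrals per survivor. If the number of controls will not be 84, state the number and recompute.

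In the analysis section, base the conclusion on the cluster-adjusted estimate with its 95% CI, and state that a non-significant result does not show that there is no difference. List the shortfall under Limitations.

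The cost is a less favourable stated figure and a few sentences. No participants are added, and neither the conduct nor the primary outcomes change.
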